#### IV. Research gap analysis:

##### 1. **Practical knowledge gap** (action-knowledge conflict gap)

Future research could consider combining ael and dj training with other types of ssc exercises to explore complementary methods for optimizing sprint and cod performance. (7)

##### 2. **Evidence gap** (contradictory evidence)

The study found that while both accentuated eccentric loading (ael) and drop jump (dj) training improved jump performance and lower body strength, there were no significant improvements in sprinting or change of direction (cod) performance. This outcome contradicts previous research and theoretical expectations that suggested these training

methods should enhance sprint and cod abilities. This inconsistency shows a gap in evidence regarding the effectiveness of ael and dj training for these specific athletic qualities.

## V. Research question:

Is there a significant effect of Effect of accentuated eccentric loading countermovement jumps and drop jump training with ladder training vs ladder training alone on sprint performance and change of direction ability in futsal players: a randomized controlled trial ?

|                         |                                                                                                         |
|-------------------------|---------------------------------------------------------------------------------------------------------|
| P (population)   | Futsal players                                                                                          |
| I (intervention) | Effect of accentual eccentric loading countermovement jumps and drop jump training with ladder training |
| C (comparison)   | Ladder training without the combined intervention                                                       |
| O (outcome)      | Sprint performance and change of direction ability                                                      |
| T (time)         | 1 year                                                                                                  |

## VI. Hypothesis:

### 1. Null Hypothesis :

H01-there will be no effect of accentual eccentric loading countermovement jumps and drop jump training with ladder training vs ladder training alone on sprint performance and change of direction ability in futsal players

H02-there will be no significant difference between effect of accentual eccentric loading countermovement jumps and drop jump training with ladder training vs ladder training alone on sprint performance and change of direction ability in futsal players: a randomized controlled trial

### Alternative Hypothesis(ha)

H1-there will be significant effect of accentual eccentric loading countermovement jumps and drop jump training with ladder training vs ladder training alone on sprint performance and change of direction ability in futsal players: a randomized controlled trial

H2-there will be significant difference between effect of accentual eccentric loading countermovement jumps and drop jump training with ladder training vs ladder training alone on sprint performance and change of direction ability in futsal players: a randomized controlled trial

## **VII. Aim of the study:**

The aim of this study is to find out of effect of accentuated eccentric loading countermovement jumps, drop jump training vs ladder training alone on sprint performance and change of direction ability in futsal players.

## **VIII. Objectives of the study:**

- To evaluate the effect of ladder training on sprint performance and change of direction ability in futsal players.
- To evaluate the effect of accentuated eccentric loading cmj, drop jump training with ladder training on sprint performance and change of direction ability in futsal players.
- To compare the effect of accentuated eccentric loading countermovement jumps and drop jump training with ladder training vs ladder training alone on sprint performance and change of direction ability in futsal players.

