|                                                                                                                                           | of low and high agility are from one another.                                                                                                     | techniques, and plyometric training methods of athletic performance skills ( $p < 0.05$ ).                                                                                                                                                                                                                                                                                                                                                                                            | athletic performance. Training techniques such as plyometric training and ladder drills are also related to agility. Applying the ladder drill and plyometric training techniques affects athletes' performance abilities. It has been demonstrated that doing plyometric and ladder drills may enhance one's athlete's performance ability. |
| Title: the effects of ladder training on sprint and change of direction performance
Author: trevor p. Short,et.al (2022) | The purpose of this study was to examine the effects of ladder training (lt) on sprint (20-m) and change of direction (cod) (l-drill) kinematics. | Fourteen basketball players were matched on baseline performance rankings and randomly assigned to a lt or conventional training (ct) group. The lt group performed all the ct exercises with the addition of 25-35 minutes of lt performed 3 times per week, for 4 weeks. Within-group analyses showed significant improvements in 20-m sprint performance from pretest to post test in lt and ct. No statistically significant difference was found in cod performance. Significant | Lt resulted in substantially greater enhancements in stride frequency (es = and ground contact time in the 20-m sprint and cod performance respectively. Lt may be more effective than ct in improving performance and kinematics. Lt should be                                                                                              |

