### **XIV. Procedure:**

Participants will be screened based on the inclusion and exclusion criteria. Individuals meeting the inclusion criteria will be recruited for the study after being informed about the purpose and nature of the study. Written informed consent will be obtained from all participants. Participants will then be randomly divided into two groups: group a and group b, with equal participants in each group.

Before the intervention, both groups will undergo baseline assessments for sprint performance and change of direction (cod) ability. Once baseline testing is completed, participants will receive their respective interventions as described below:

- Group A: Accentuated eccentric loading (AEL) countermovement jumps, drop jump training with ladder training.
- Group B: Ladder training only.

Group A will receive accentuated eccentric loading (AEL) countermovement jumps and drop jump training with ladder training and Group B will receive Ladder training.

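### Objectives 1 and 2 ask for effects that a two-arm add-on design cannot identify, and the aim leaves ladder training out of Group A

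*Protocol*

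**What the plan says.** The Procedure (section XIV) defines two arms and no others: "Participants will then be randomly divided into two groups: group a and group b, with equal participants in each group". Their content is "Group A: Accentuated eccentric loading (AEL) countermovement jumps, drop jump training with ladder training" and "Group B: Ladder training only". In the two intervention tables, the ladder component is the same for both groups: the same drills in each two-week block, 6 repetitions by 2 sets, the same rests, and 3 sessions per week.

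Section VIII lists three objectives. The first is "To evaluate the effect of ladder training on sprint performance and change of direction ability in futsal players". The second asks for the effect of the whole Group A package on the same outcomes. The third compares the two groups.

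The aim (section VII) is to find the "effect of accentuated eccentric loading countermovement jumps, drop jump training vs ladder training alone on sprint performance" and change of direction. Here Group A is described without ladder training. The research question (section V) describes the comparator as "Ladder training without the combined intervention".

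Outcomes are measured before and after the 6 weeks in each group (section XVII.1 and Annexure II). Section XVII.3 names the two groups as the comparison and gives a t-test or a Mann-Whitney U test. It names no paired test.

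**The concern.** An objective to evaluate the effect of an intervention is a causal claim, and in a randomised trial it should rest on a contrast between arms that differ in that intervention. Ladder training does not differ between these arms, so randomisation contributes nothing to objective 1. Objective 2 needs a group without the package that is also free of ladder training, and there is none.

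The protocol's own literature review shows why a within-arm change is a weak substitute. In the cited ladder trial in basketball players, "Within-group analyses showed significant improvements in 20-m sprint performance from pretest to post test in lt and ct". The arm without ladder work also improved. That trial could at least compare its two arms on ladder training; this one cannot.

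At stake is what may be concluded. A report written to these objectives could present one group's improvement as evidence that ladder training, or the package, works. The aim, read literally, sets jump training against ladder training, a comparison that no pair of arms provides.

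**Working it through.** **What each arm's change contains.** Let D be the change that would occur over 6 weeks with neither programme (test practice, ongoing futsal, regression to the mean), L the effect of ladder training, and J the effect of adding the jump programme to ladder training.

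- Group A change = D + L + J
- Group B change = D + L
- Group A minus Group B = J

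| Statement | Quantity wanted | What the design gives |
|---|---|---|
| Objective 1 | L | D + L (Group B change) |
| Objective 2 | L + J | D + L + J (Group A change) |
| Objective 3 | J | J (randomised contrast) |
| Aim as worded | jumps without ladder versus ladder | no arm does jumps without ladder |

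Only objective 3 is free of D. L cannot be separated from D without an arm that omits ladder training.

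**The aim against the rest of the protocol.** The title, the research question, H01 to H2, objective 3, the independent variables, the Procedure and the comparison groups in section XVII.3 all give Group A ladder training. The aim alone does not.

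**Illustration of how far D could mislead.** Inputs from the protocol (section IX): 28 per group, SD 0.125 s, and a planning change of 0.064 s listed beneath a pre mean and a post mean. The 28 is taken as stated. The protocol's own formula gives 2 × (1.96 + 1.64)² × 0.125² / 0.064² = 98.9 per group, but that is a separate matter and does not bear on this point.

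Assumptions not in the protocol: a drift D of 0.032 s (half the planning change) or 0.064 s (all of it), no training effect, and a pre-post correlation r of 0.3 to 0.75. The upper value matches the top of the only sprint-timing reliability that the protocol quotes, an ICC of 0.60 to 0.75 for manual timing (section XVI).

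Formulas: SD of change = 0.125 × √(2(1 − r)); noncentrality = D × √28 / SD of change; two-sided 5% paired t-test on 27 degrees of freedom, critical value 2.052.

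| r | SD of change (s) | Noncentrality at 0.032 s / 0.064 s | Significant at 0.032 s | Significant at 0.064 s |
|---|---|---|---|---|
| 0.3 | 0.148 | 1.14 / 2.29 | 20% | 60% |
| 0.5 | 0.125 | 1.35 / 2.71 | 26% | 74% |
| 0.6 | 0.112 | 1.51 / 3.03 | 31% | 83% |
| 0.75 | 0.088 | 1.92 / 3.83 | 46% | 96% |

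The nominal rate is 5%. With a much smaller drift of 0.01 s the same calculation gives 6% to 9% over this range of r, so the size depends heavily on the drift assumed.

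**The case against.** The strongest reply is that the trial is an ordinary add-on trial with a few loose sentences. Much of this stands.

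- **No within-arm test is planned.** A reader might infer that the protocol commits to reporting that ladder training improves sprint time. It does not. Section XVII.3 names a between-group test, and its t-test sentence does not say what is compared. The objectives leave room for such a claim but do not prescribe it, and the percentages above belong to a test that the protocol never specifies.
- **The aim is an isolated slip.** Every other statement of the question has the add-on contrast. To report jumps as better than ladder work, an author would have to ignore all of them. It is still the formal aim and should be right.
- **H01 and H1 might look like single-arm claims.** As worded, each compares the package with ladder training alone. They duplicate H02 and H2 loosely but point to the randomised contrast, and making them descriptive would be a step backwards.
- **Extra work and bundling.** Group A does 4 × 8 × 2 = 64 to 4 × 10 × 2 = 80 jumps per session with no counterpart in Group B. A reader might infer that objective 3 is flawed because it cannot separate the two jump types or the added volume. But the research question and the variables treat the programme as one combined intervention, so no stated objective is contradicted.
- **The cited ladder trial does not measure drift.** Its comparison arm did conventional training, so its gain is not change without training. It shows only that improvement within a ladder arm need not come from the ladder work.

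What the reply does not remove is the wording of objectives 1 and 2. They ask for effects, and the named between-group test cannot supply them.

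**Conclusion.** The point holds as a fault in the stated objectives and aim, not in the randomised comparison. Objectives 1 and 2 claim effects for which the trial offers only uncontrolled change, and the aim contradicts the arms. Objective 3 is sound as an add-on question. This follows from the arm definitions alone and needs no assumption.

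The size is illustrative: about 20-46% false significance for a 0.032 s drift and 60-96% for 0.064 s, with 28 players, SD 0.125 s and r from 0.3 to 0.75. Neither the drifts nor the correlations come from the protocol. Higher figures could be had by assuming r = 0.9, but the quoted reliability of manual timing gives no support for that.

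**What to change.** 1. Reword objectives 1 and 2 as one descriptive objective: to describe the pre-to-post change in each group, reported as mean change with 95% confidence interval and with no claim of a training effect.
2. Make objective 3, the randomised add-on contrast, the only effectiveness objective.
3. Reword the aim so that it compares AEL countermovement jumps and drop jumps added to ladder training with ladder training alone, in line with the title and the group definitions.
4. Leave H01 and H1 as between-arm contrasts. If the hypotheses are edited, merge them with H02 and H2.

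The cost is protocol wording only, with no added participants, visits or tests. The downside is that two objectives become descriptive. A causal answer on ladder training itself would need an arm without it, which is a different trial.

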## **IX. Methodology:**

**Study type:** Experimental study

**Study design:** Randomised controlled trial (RCT)

**Target population:** Futsal players

**Sampling technique:** Simple random sampling

**Duration of study:** 1 year

**Allocation ratio:** 1:1

**Blinding:** Single blinded (participants will be blinded)

**Study setting :** futsal turfs across dmiher , Sawangi Meghe Wardha

**Study population:** recreational and competitive futsal players

**Sample size:** the sample size for this study was determined using g\*power (version 3.1.9.4, heinrich heine universität düsseldorf, düsseldorf, germany), a statistical software that facilitates power analysis and sample size estimation based on various statistical tests.

formula using mean difference

$$n1 = n2 = 2 \times [(z\alpha + z\beta)^2 \times \sigma^2] / (\delta^2)$$

Where:

- $Z\alpha = 1.96$  (considering ci at 95%)
- $Z\beta = 1.64$  (power at 95%)

**Primary variable:** 30 m sprint

- Mean  $\pm$  sd (pre) result on 30 m sprint in tbi readings =  $4.36 \pm 0.12$
- Mean  $\pm$  sd (post) result on 30 m sprint in tbi readings =  $4.29 \pm 0.13$
- Mean difference ( $\delta$ ) = 0.064
- Pooled standard deviation = 0.125

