## **XI. Tools and instrument**

1. **Measuring tape:** used to mark accurate distances for sprint and agility tests.
2. **Cones/markers:** define start/finish lines and layouts for agility tests.
3. **Stopwatch:** manual timing alternative for sprints and agility drills.
4. **Dumbbells for accentual eccentric loading:** used to provide controlled resistance during the lowering (eccentric) phase of countermovement jumps, emphasizing gradual muscle lengthening under load.
5. **Agility ladder:** used for ladder drills to enhance agility and footwork.
6. **Video cameras:** record movements for biomechanical analysis of speed and cod.
7. **T-test setup:** standardized cone layout for lateral and forward cod assessment.
8. **Data sheets:** for recording, organizing, and analysing performance data.

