### **XIII. Eligibility criteria:**

➤ **Inclusion criteria:**

- (1) Age between 18-30 years
- (2) BMI-18.5–24.9
- (3) Regular participation in futsal activities since 1 year.
- (4) Recreational and competitive futsal players participating in regional, national, or professional leagues
- (5) Willingness to participate in a structured 6-week intervention program focusing on accentuated eccentric loading  
Countermovement jumps, drop jump training, and ladder drills.

➤ **Exclusion criteria:**

- (1) presently having pain due to trauma associated to lower limb
- (2) laxity of articular ligaments or meniscus injury around knee
- (3) recent history of dislocation of patella or recent fracture
- (4) chondromalacia patella
- (5) existing progressive neurological conditions
- (6) plantar fasciitis

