### Group A:

Accentuated eccentric loading Countermovement jump, drop jumps with Ladder training

| Exercise category                                         | Procedure:                                                                                                                                                                                                                                                                                                                            | Reps/sets and duration                                                                                           | Progression                                                                                                                                |
|-----------------------------------------------------------|---------------------------------------------------------------------------------------------------------------------------------------------------------------------------------------------------------------------------------------------------------------------------------------------------------------------------------------|------------------------------------------------------------------------------------------------------------------|--------------------------------------------------------------------------------------------------------------------------------------------|
| Accentuated eccentric loading (ael) countermovement jumps | 

- use dumbbells or a weighted harness for eccentric loading.

- perform countermovement to approximately 90° knee flexion.

- drop the load before the concentric phase for maximal jump.

                                                                               | Weeks 1-3: 4 sets of 8 repetitions
weeks 3-6: 4 sets of 10 repetitions
(3 sessions per week) | Start with 10-20% of body mass as additional eccentric load, progressively increasing based on tolerance. Rest: 2 minutes between sets.    |

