| Drop jump training                                        | Procedure: 

- step off the box without jumping.

- land softly on the balls of the feet and immediately perform a vertical jump.

                                                                                                                                         | Weeks 1-3: 4 sets of 8 repetitions
weeks 3-6: 4 sets of 10 repetitions
(3 sessions per week) | Drop height: begin with 30 cm, progressing to 50 cm as tolerated. Rest: 2 minutes between sets.                                            |
| Ladder training                                           | Drills: 

- weeks 1-2: straight run, hopscotch, single-foot hops zigzag pattern.

- weeks 3-4: two-foot run, backward hopscotch, single-foot lateral in/out hops.

- weeks 5-6: bunny hops, hopscotch variation, two-foot hops zigzag pattern

 | 6 repetitions of each drill x 2 sets per session.
(3 sessions per week)                                       | Rest: 30 seconds between repetitions, 60 seconds between sets. Focus on quick ground contact, coordination, and multidirectional movement. |

**Group B:** control group

| Exercise category      | Procedure:                                                                                                                                                                                                                                                                                  | Reps/sets and duration                                                         | Progression                                                                                                                                              |
|------------------------|---------------------------------------------------------------------------------------------------------------------------------------------------------------------------------------------------------------------------------------------------------------------------------------------|--------------------------------------------------------------------------------|----------------------------------------------------------------------------------------------------------------------------------------------------------|

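### The protocol declares participants blinded, which two visibly different training programmes rule out, and it states no blinding of the person who conducts and times the tests

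*Protocol*

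**What the plan says.** Section IX (Methodology) gives the blinding as "Single blinded (participants will be blinded". Participants are the only party named.

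Section XIV (Procedure) defines the arms as "Group A: Accentuated eccentric loading (AEL) countermovement jumps, drop jump training with ladder training" and "Group B: Ladder training only". The exercise tables tell Group A to "use dumbbells or a weighted harness for eccentric loading" and, for the drop jumps, to "step off the box without jumping". The ladder drills are the same in both arms. Group B's table has no other entry and describes no sham or matched activity.

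Inclusion criterion 5 (section XIII) requires "Willingness to participate in a structured 6-week intervention program focusing on accentuated eccentric loading" and goes on to name countermovement jumps, drop jump training and ladder drills. Section XIV says candidates are recruited "after being informed about the purpose and nature of the study".

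Sections XVI and XVII make the 30 m sprint and the agility T-test the primary outcomes. The materials list (section X) allows either a stopwatch or timing gates. The tools list (section XI) includes a stopwatch, described as a "manual timing alternative for sprints and agility drills", and no gates.

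**The concern.** A player who spends six weeks on ladder drills without a loaded jump or a box knows that the jump components were not assigned to him or her. The declared blinding is a property this design cannot have, and a report that repeats it would be untrue.

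The line also uses up the single blind on the party who cannot be blinded. The blind that could be kept, that of the person who runs and times the tests, is not mentioned. Both outcomes depend on maximal effort and may depend on a hand on a stopwatch. A difference between arms in effort, encouragement or timing would pass directly into the treatment comparison. Because the target difference is small, a small shift could matter.

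**Working it through.** **Can participants be blinded?** The relevant statements, side by side:

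| Element | Group A | Group B |
|---|---|---|
| Countermovement jumps with dumbbells or harness | yes | no |
| Drop jumps from a box | yes | no |
| Ladder drills | yes | yes, same drills |
| Sham or matched activity | not applicable | none described |
| Components named in criterion 5 | all three | all three |

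The content of the sessions reveals the arm. Criterion 5 adds that all candidates must be willing to do a programme with all three components, so a Group B player has a ready reference for what is absent. Keeping players unaware of the hypothesis alone is not described, and it would fit poorly with explaining the purpose of the study before recruitment.

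**Is anyone else blinded?** Section IX names participants only. The visible sections on outcomes, data collection, statistical method and monitoring state no blinding of the tester.

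**How much could it matter?** Inputs from section IX: target difference 0.064, SD 0.125, starting mean 4.36, 28 per group, two-sided 5% (z = 1.96). The unit is taken as seconds, as on the Annexure II sheet.

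Target relative to the sprint time: 0.064 / 4.36 = 1.5%.

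The size of a bias is not in the documents, so a range b = 0.01 to 0.05 s is assumed. With no true effect, the rejection rate is P(|Z + b/SE| > 1.96), where SE = SD × √(2/n).

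- n = 28: SE = 0.125 × √(2/28) = 0.0334
- n = 99: SE = 0.125 × √(2/99) = 0.0178

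| Assumed shift b (s) | b / 0.064 | b / SE at n = 28 | False-positive rate, 28 per group | False-positive rate, 99 per group |
|---|---|---|---|---|
| 0.01 | 16% | 0.30 | 6.0% | 8.7% |
| 0.02 | 31% | 0.60 | 9.2% | 20.3% |
| 0.03 | 47% | 0.90 | 14.6% | 39.3% |
| 0.05 | 78% | 1.50 | 32.2% | 80.4% |

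The 99 comes from checking the plan's own sample size. The printed formula with its printed inputs, 2 × (1.96 + 1.64)² × 0.125² / 0.064², gives 98.9, not 28. That is a separate matter. It is relevant here only because it shows that enlarging the trial does not help: the bias stays the same while the standard error shrinks.

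The protocol gives no corresponding planning figures for the agility T-test, so this arithmetic covers the sprint only.

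**The case against.** The participant-blinding line itself is hard to defend, but four stronger readings are tempting and need limits.

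- *The timekeeper knows the allocation.* A reader might infer this from a single blind that names only participants. No sentence says who times the tests, who delivers training, or what the tester knows. What stands is that assessor blinding is not stated. Blinding belongs in the protocol, so a separate analysis plan would not normally supply it.
- *Both tests are timed by a human.* Section X allows timing gates, and section XVI calls fully automated systems the most accurate. Hand timing is possible, not established. Equally, the protocol does not commit to gates, and gates would not remove differences in effort or encouragement.
- *The bias could exceed the effect sought.* Nothing in the documents supports this. Section XVI reports an ICC of 0.60 to 0.75 for manual timing, with significant reaction-time error. That concerns reliability, and unreliability alone adds noise equally to both arms. It gives neither size nor direction for a difference between arms.
- *Every player is told about all three components at entry.* Criterion 5 and the disclosure in section XIV make this likely, but the consent forms (Annexure III) were not available to confirm it. The visible difference between the programmes carries the conclusion without it.

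It is also fair to say that no estimate, test or sample size in the plan depends on the blinding line.

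**Conclusion.** The point holds in two parts of unequal strength. Firmly: the statement that participants are blinded contradicts the interventions in the same protocol and should not stand. Less strongly, because it rests on silence: no assessor blinding is stated for outcomes that are open to influence by the tester.

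The possible size is illustrative. Under assumed shifts of 0.01 to 0.05 s, the bias would be a material fraction of the target difference, but below it. The inflated false-positive rates rest on those assumed shifts, on the printed SD and group size, and on a normal approximation. The change should be made; it is a wrong label and a missing safeguard, not evidence that the results will be biased.

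**What to change.** Replace the blinding line in section IX with: *Participants and trainers are not blinded; the outcome assessor is blinded to allocation.* Then add to the procedure:

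- The team member who times and records the pre- and post-tests does not deliver or attend training and is not told the allocation.
- Players are asked not to reveal their group to that person.
- The timing gates already in the materials list are used where available.
- Reports do not describe the trial as participant-blinded, and they name possible differences in player effort as a limitation, since assessor blinding does not remove these.

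The cost is protocol wording and a division of tasks. The assessor must stay away from three sessions a week for six weeks. Annexure I has signature lines for an investigator and a co-investigator, so a split is plausible, but the protocol assigns neither of them to training or testing. The team must confirm that it can be staffed. No training content changes.
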